The intervention focussed on a central role model character the “*MaaChampion*”, a mother, who practises the key behaviours used in the messages (Table 1) and encourages other mothers to do the same. Village mothers could achieve “*MaaChampion*” status if they demonstrated the same. Other components such as competitions (for mothers of children <5 years) and environmental cues were designed to embed behaviour change. The intervention was delivered to the entire population but focussed on mothers with children under-5 years in each village. It consisted of the team visiting each village on days 1, 2, 17 and 25, delivered between February and April 2015 (the dry season). A fifth visit took place after six months since we envisaged that if such a programme is to be implemented at scale, then to sustain behaviour change, villages would need a reminder visit before or early in the diarrhoea high-risk rainy season (if several months after the initial four day campaign), a time when mothers and their families are busy with farm work and may forget weaning-food hygiene behaviours. The programme’s daily schedule is summarised in Tables 2.

Implementation was staggered over two months. The intervention team logged significant events, comments and overall participation of villagers/mothers in the programme that helped guide the process evaluation of the intervention implementation.

The control villages were given a day's health education campaign on water use in domestic vegetable gardening. A public health officer held community meetings explaining the campaign using a flipchart.

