|                      | Afternoon event at a central point for all villagers: Through drama, videos and quizzes to impart the primary purpose and the 6 messages; obtain pledges from mothers to commit to practice the promoted behaviours and aim to become MaaChampion .                                                                                                                                                                                     |
|                      | New community volunteers ( MaaSupervisors ) training to encourage and visit/supervise mothers of <5yr children.                                                                                                                                                                                                                                                                                                                                       |
| 2                    | Meeting Alkalo & announce to villagers the presence of the team.                                                                                                                                                                                                                                                                                                                                                                                             |
|                      | House-to-house visit with MaaSupervisors to check on mother's understanding & adherence to practices; promotion of mothers to MaaFambo or MaaChampions .                                                                                                                                                                                                                                                                  |
|                      | Ad-hoc women or men meeting held separately in neighbourhoods to reinforce messages through stories and demonstrations.                                                                                                                                                                                                                                                                                                                        |

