## **2. Protocol for the second evaluation of clusters at 2-year follow-up investigating the effect of weaning-food hygiene community intervention in rural Gambia**

### **Introduction**

The objective is to ascertain any residual effect from the intervention for all the outcome measures at 30-months follow-up since the 4 days campaign activities and 2-year follow-up since the reminder 5th-month visit was carried out. (Intervention was village visits on days 1,2,17,25 and volunteer home visits in between, constituting the main intervention hereafter called the 4-day village campaign visits, plus a reminder visit at the 5th-month after these initial 25 days).

For the main cRCT outcome measures, the procedure for evaluation at 6-months will be repeated by a new recruit of 26 female data collectors who will be trained as with the previous group of data collectors at 6month. The same tools will be used with minor changes for 2 years as appropriate. However, some additional secondary research questions and sub-studies with respect to the index child and adults have been added as described below. Two nested studies took place at the same time also which helped to mask the data collection for the trial outcomes.

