### **2.1.3 The population sample of mothers per village for 2 years evaluation data**

**(including additional variables in 2.1.1 and 2.1.2)**

We aim to select mothers who are currently weaning or have children who may have a combination of weaning and family food (E.g. 24-36month old children). As such some will be those who would not have been pregnant or had an infant at the time of the 4-days campaign visits or the 5th-month reminder.

For sampling frame, as with the 6-month follow-up the baseline list of children in the villages will be updated using the maternal-child health register and village health worker's list of children in each village. From these there will be 26 mothers chosen from each of the control and intervention villages. Sample size will be 23-26 mothers per cluster (as suppose to the target of 20 at the 6-month follow-up) because as indicated in the 6-month sample size calculation a minimum of 12 mothers per cluster of weaning children is needed (see above sample size for 6-month follow-up) but at 2 years we have 2 groups of mothers: new mothers and those who are mothers at the time of the 4-days campaign activities. (New mothers at 2-year follow-up are those with children 6-25month who will be eating weaning-food. Children aged 26-36 months will still, for the most part, be eating weaning-food at 2-year follow-up plus some of the family-food. Their mothers would have been pregnant during the 4-days campaign visits of the intervention in December to February 2014 and ready to wean at the 5th-month reminder visit. This population are the candidates most likely to *remember and practice* the hygienic behaviours while still *making* weaning-food during the 2-year assessment.) Therefore, we aim to have approximately 12 of each sub-group of mothers recruited. All individual mothers or main carers of children 6 to 36 months living in the village for a minimum of 2 years will be eligible for selection but mothers who are not available for cooking the child's weaning-food during the 2-year evaluation visit will be

excluded. (All mothers were available for the 6-month evaluation survey so we envisage very few or no mothers will be excluded).

To capture all these sub-groups of mothers, the selection of the mothers will be stratified as follows:

1. All mothers of children age 18 to 24 months will be chosen.
2. The rest of the mothers will be chosen according to the following formula:

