$$x = \frac{(26 - \text{all mothers with 18 to 24 month old children})}{2}$$
3. Then,  $x$  number of mothers with children aged 6-18 months and  $x$  number of mothers with children aged 24-36 months will be randomly chosen from the list.

For sub-group analysis, ‘New mothers’ will be classified as those with children 6-25m since these mothers would not have had a child at before the 5th village reminder visit and the 6-month evaluation and so as mothers were not a part of the MaaChampion program when any part of the intervention was taking place in the villages.

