#### **2.1.4 Blinding/masking at assessment**

Further to the masking during assessment at 6-months, the same methods were employed to mask the assessment team and mothers to the 32-month data collection purpose as follows:

- Reduction of the study population’s exposure to the trial procedures (using random cross-sectional samples to observe mother’s behaviours on only 3 occasions, baseline, 6 and 32 months).

- Using different research teams and methods for baseline and each of the evaluation rounds: For baseline, male researchers surveying the mother with a short questionnaire at the door, and two different teams of female data-collectors.
- Ensuring the baseline, 6- and 32-month evaluation teams stayed only one day in each village, and thus mothers were unable to discuss assessor procedures between data collection days.
- Concealment of the purpose of 6- and 32-month evaluations from mothers and data-collectors by conducting a larger evaluation of water and food utilisation in households and health related measures. This was facilitated as follows:
  - During training and consent from mothers describing the survey/observations as a larger evaluation of water and food utilisation in households and health related measures.
  - Not informing the data-collectors that an intervention and a trial has taken place.
  - Concealment of weaning-food evaluation assessments tools within a larger assessment of food and water usage observation and questionnaire tools. At 32-months additional questions and formats related to observing the child behaviour/play, ARI health economics, and details of water sources were added to the 6-month tool.
  - Consenting the mothers for this larger evaluation and not for the weaning-food safety and hygiene trial
  - Concealment from mothers and data-collectors aided by the fact that other government, NGO, and UN agencies and MRC Gambia have numerous concurrent nutrition/WaSH intervention programmes, studies and surveillance sites in this region resulting in numerous visits to villages for interventions and data collection. In terms of intervention material in the villages, if some posters or village banners related to weaning-food safety

and hygiene remained, these would have been simultaneous with other intervention activity posters and banners related to other agency programmes as is prevalent in LMIC rural communities.

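### 'New mothers' are defined by the index child's age alone, so the subgroup mixes women the campaign had targeted with women it had not, and cannot be read as an effect in non-participants

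*Protocol*

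**What the plan says.** Protocol section 2.1.3 splits the mothers surveyed at 2 years into two groups: new mothers, and those who were already mothers at the campaign. It aims for about 12 of each per village. The rule is the index child's age: 'new mothers' "will be classified as those with children 6-25m since these mothers would not have had a child at before the" reminder visit, "so as mothers were not a part of the MaaChampion program when any part of the intervention was taking place in the villages". Neither parity, older children nor attendance enters the rule. Eligibility requires at least 2 years' residence in the village. Section 2.1.5 plans a subgroup analysis of the effect in this group and names no other subgroup.

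Section 1.2.2 describes the target population: "The intervention was delivered to the entire population but focussed on mothers with children under-5 years in each village". The competitions were for mothers of under-5s. Table 2 lists, for the first visit, volunteer "training to encourage and visit/supervise mothers of <5yr children".

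The dates behind the age cut vary. The campaign is "delivered between February and April 2015 (the dry season") in section 1.2.2, but section 2.1.3 refers to "visits of the intervention in December to February 2014". The survey is "at 30-months follow-up since the 4 days campaign activities" in the Introduction to part 2, while section 2.1.4 masks "mothers to the 32-month data collection purpose as follows". The reminder is at the fifth month in part 2 and after six months in section 1.2.2.

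**The concern.** The step from a young index child to a woman who was not part of the programme holds only if that child is her first, or if all her older children were past 5 at the visits. A woman with a toddler in 2015 and another baby since was within the campaign's stated focus: home visits, competitions and the chance of MaaChampion status. The rule still puts her in the group described as outside the programme.

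What is at stake is how one planned result is read. A positive effect in 'new mothers' would naturally be taken as an effect in women who had no part in the programme. With the group mixed in unknown proportion, it could come partly or wholly from women the campaign had targeted.

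**Working it through.** The Protocol states no figure for this point, so there is none to reproduce. The check is date arithmetic, then two illustrations.

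**1. Who was a target despite a young index child?** Inputs: index child 6-25 months (section 2.1.3); campaign 30 months before the survey (part 2, Introduction) or 32 (section 2.1.4); reminder 5 months after the campaign (part 2, Introduction); target group mothers of children under 5 (section 1.2.2, Table 2).
- On 30-month timing the index child was born between 30 − 25 = 5 and 30 − 6 = 24 months after the campaign.
- An older sibling alive and under 5 at the campaign is now aged between 30 and 60 + 30 = 90 months.
- At the reminder, 30 − 5 = 25 months before the survey, the range is 25 to 60 + 25 = 85 months.
- Together, a woman with another child now aged about 25 to 90 months was a target at one visit or more, if she lived in the village then. On 32-month timing the upper limit is 60 + 32 = 92.

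The age rule therefore does not establish that a woman was outside the programme.

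**2. What mixing could do (illustration).** Let f be the share of the group that had been targeted. Apparent effect = f × (effect in targeted women) + (1 − f) × (effect in the others). The Protocol does not give f. Assume 25 points (the design difference in section 1.2.6) in targeted women and 0 in the others:

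| f (assumed) | Apparent effect, points | Untargeted women of 12 per village |
|---|---|---|
| 25% | 6.25 | 9.0 |
| 50% | 12.5 | 6.0 |
| 75% | 18.75 | 3.0 |
| 90% | 22.5 | 1.2 |

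With 15 clusters per arm, 12 mothers per cluster, ICC 0.04 and cluster-size CV 0.22, power to detect 12.5 points above 11.3% is about 73-74%. So at f = 50% a significant 'new mother' effect would be likely even with no effect in untargeted women.

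**3. How much does the age cut depend on the dates?**
- 30 − 5 = 25 months since the reminder, which matches the 25-month cut.
- The 2-year label implies 24 months. Index children aged 24-25 months were then already born at the reminder, against the stated reason.
- 32 − 5 = 27 months. Children aged about 26-27 months were then born after the reminder but fall in the other group.

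These shifts are a month or two at the boundary. They are minor beside step 1.

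**4. Size and power of a stricter subgroup.** If 20-30% (assumed) of the planned 12 are first-time mothers, m = 0.2 × 12 = 2.4 to 0.3 × 12 = 3.6 per village. Design effect = 1 + [(1 + 0.22²)m − 1] × 0.04; effective n per arm = 15m / design effect. Rates are 11.3% v 36.3%, with unpooled variance 0.1005 + 0.2313 = 0.3318:
- m = 2.4: design effect 1.061, effective n 33.9, SE = √(0.3318/33.9) = 0.0989, z = 0.25/0.0989 = 2.53, power = Φ(2.53 − 1.96), about 71%.
- m = 3.6: design effect 1.111, effective n 48.6, SE 0.0826, z = 3.03, power about 86%.

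With a pooled null variance these become about 68% and 84%. For a 12.5-point difference the unpooled figures are about 28% and 38%.

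**The case against.** Several parts of the other side stand.

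- **Purpose.** A reader might infer that the subgroup is meant to demonstrate spread to women who never took part, and would be reported so. The Protocol does not say this. Section 2.1.5 speaks only of the effect in new mothers, and the 2-year objective is residual effect. The fault is in the non-exposure statement itself, not in a declared claim of diffusion.
- **Size.** A reader might also infer that most 'new mothers' had been targeted, or that the result would be spurious. The share is unknown. A zero effect in the other women is an extreme assumption, since the whole village received the campaign. The residence rule asks for only 2 years while the campaign was 30-32 months earlier, so some women with older children arrived after it. Being a target is also not the same as taking part.
- **Dates.** The 25-month cut agrees with 30 − 5. The calendar conflict needs reconciling but does not by itself undermine the subgroup.
- **A stricter definition is imperfect.** Having no under-5 child at the visits is not identical to being a first-time mother. First-time mothers are also likely to be younger and less experienced, and may have attended village-wide events.

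One reading does not rescue the text: that the women were not in the programme as mothers of this particular child. Sections 1.2.2 and Table 2 define the targets by any child under 5, and section 2.1.3 contrasts the group with women who were mothers at the campaign.

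**Conclusion.** The concern holds as a matter of definition and interpretation. Index-child age alone does not show that a woman was outside the programme, and the Protocol's own account of the targets contradicts that statement for women with an older under-5 child. The subgroup therefore mixes targeted and untargeted women in a proportion the Protocol does not give.

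The randomised comparison within the group remains valid, because the same age rule applies in both arms, and the main 2-year analysis is untouched. What the result cannot support is a reading as the effect in mothers who were not part of the programme. The 6.25 to 22.5 points above illustrate how far it could mislead. They rest on assumed shares of 25-90%, a 25-point effect in targeted women and none in the rest, and they are not estimates of bias.

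**What to change.** 1. Rename the group 'index child born after the reminder visit' and delete the statement that these women were not part of the programme. This costs only wording.
2. Where parity (already a planned covariate in section 1.2.11) or the village child lists allow, add a subgroup or sensitivity analysis in which a new mother is a woman with no child under 5 in the village at any campaign or reminder visit. Report the arm-by-subgroup interaction as exploratory, noting that age and experience differ between the groups and that village-wide events reached everyone.
3. Reconcile the campaign dates (sections 1.2.2 and 2.1.3), the reminder timing (fifth month or after six months) and the survey interval (30 or 32 months), and set the age cut from the logged visit dates.

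The cost of item 2 is precision. At the planned 12 per village, power is about 71-86% for 25 points under the assumed 20-30%, and far lower for smaller effects. If parity or siblings' birth dates were not recorded and can no longer be obtained, items 1 and 3 still suffice to make the reported subgroup accurate.

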#### **2.1.4 Blinding/masking at assessment**

Further to the masking during assessment at 6-months, the same methods were employed to mask the assessment team and mothers to the 32-month data collection purpose as follows:

- Reduction of the study population’s exposure to the trial procedures (using random cross-sectional samples to observe mother’s behaviours on only 3 occasions, baseline, 6 and 32 months).

- Using different research teams and methods for baseline and each of the evaluation rounds: For baseline, male researchers surveying the mother with a short questionnaire at the door, and two different teams of female data-collectors.
- Ensuring the baseline, 6- and 32-month evaluation teams stayed only one day in each village, and thus mothers were unable to discuss assessor procedures between data collection days.
- Concealment of the purpose of 6- and 32-month evaluations from mothers and data-collectors by conducting a larger evaluation of water and food utilisation in households and health related measures. This was facilitated as follows:
  - During training and consent from mothers describing the survey/observations as a larger evaluation of water and food utilisation in households and health related measures.
  - Not informing the data-collectors that an intervention and a trial has taken place.
  - Concealment of weaning-food evaluation assessments tools within a larger assessment of food and water usage observation and questionnaire tools. At 32-months additional questions and formats related to observing the child behaviour/play, ARI health economics, and details of water sources were added to the 6-month tool.
  - Consenting the mothers for this larger evaluation and not for the weaning-food safety and hygiene trial
  - Concealment from mothers and data-collectors aided by the fact that other government, NGO, and UN agencies and MRC Gambia have numerous concurrent nutrition/WaSH intervention programmes, studies and surveillance sites in this region resulting in numerous visits to villages for interventions and data collection. In terms of intervention material in the villages, if some posters or village banners related to weaning-food safety

and hygiene remained, these would have been simultaneous with other intervention activity posters and banners related to other agency programmes as is prevalent in LMIC rural communities.

- No contact between the study or intervention team and the villages between 6- and 32-month follow-up. This meant that at 32-months, both control and intervention villages were equally unlikely to link the 32-month evaluation with the weaning-food and hygiene programme having not had any reminders or contact for over 2 years and that the families were mostly ‘new mothers’.

### **2.1.5 Statistical analysis for 2 years evaluation data (including additional variables in 2.1.1 and 2.1.2)**

The statistical analysis plan for the analysis of the 2-year follow-up evaluation data will follow the same analysis plan described earlier for the 6-month follow-up evaluation data.

Sub-group analysis will be performed to establish the effect on the ‘new mothers’.

All analyses will be conducted using Stata 15.

## **2.2 Qualitative Studies:**

**2.2.1 Background:** Often community participation programmes are not assessed for the success of individual elements. We hope that this assessment will guide us to improve and expand the successful elements of the programme.

**2.2.2 Objectives:** The objectives of this qualitative process assessment are to investigate the elements of the intervention the villagers felt were most effective and attractive/memorable to them (encouraging them to attend the village meetings), and what messages they still retain.

**2.2.3 Methods:** After the new independent quantitative data collector team have finished visiting the villages for evaluation, focus group discussions (FGD) will be conducted with mothers, grandmothers, and fathers in 3 or 4 intervention villages, One FGD will be held with Alkalos and one will be held with TBAs brought together from 6-10 intervention villages (total 11-14 FGD depending on saturation of themes emerging from mothers/grandmothers/father's FGDs).

FGDs will be conducted by 2 trained researchers not involved in the intervention or 6-month and 2-year follow-up. They will be conducted in the local languages and facilitated by a researcher who speaks these languages fluently. These discussions will be audio recorded and later transcribed/translated into English. Anonymised clips of audio recordings will then be sent to an independent language interpreter to validate translation. Translated FGD data will be analysed thematically by independent researchers. NVIVO software will be used to assist with data analysis.

